## Abstract

**Background:**

During open heart surgery, patients are connected to a heart-lung bypass machine that pumps blood around the body (“perfusion”) while the heart is stopped. Typically the blood is cooled during this procedure (“hypothermia”) and warmed to normal body temperature once the operation has been completed. The main rationale for “whole body cooling” is to protect organs such as the brain, kidneys, lungs, and heart from injury during bypass by reducing the body’s metabolic rate and decreasing oxygen consumption. However, hypothermic perfusion also has disadvantages that can contribute toward an extended postoperative hospital stay. Research in adults and small randomized controlled trials in children suggest some benefits to keeping the blood at normal body temperature throughout surgery (“normothermia”). However, the two techniques have not been extensively compared in children.

**Objective:**

The Thermic-2 study will test the hypothesis that the whole body inflammatory response to the nonphysiological bypass and its detrimental effects on different organ functions may be attenuated by maintaining the body at 35°C-37°C (normothermic) rather than 28°C (hypothermic) during pediatric complex open heart surgery.

**Methods:**

This is a single-center, randomized controlled trial comparing the effectiveness and acceptability of normothermic versus hypothermic bypass in 141 children with congenital heart disease undergoing open heart surgery. Children having scheduled surgery to repair a heart defect not requiring deep hypothermic circulatory arrest represent the target study population. The co-primary clinical outcomes are duration of inotropic support, intubation time, and postoperative hospital stay. Secondary outcomes are in-hospital mortality and morbidity, blood loss and transfusion requirements, pre- and post-operative echocardiographic findings, routine blood gas and blood test results, renal function, cerebral function, regional oxygen saturation of blood in the cerebral cortex, assessment of genomic expression changes in cardiac tissue biopsies, and neuropsychological development.

**Results:**

A total of 141 patients have been successfully randomized over 2 years and 10 months and are now being followed-up for 1 year. Results will be published in 2015.

**Conclusions:**

We believe this to be the first large pragmatic study comparing clinical outcomes during normothermic versus hypothermic bypass in complex open heart surgery in children. It is expected that this work will provide important information to improve strategies of cardiopulmonary bypass perfusion and therefore decrease the inevitable organ damage that occurs during nonphysiological body perfusion.

**Trial Registration:**

ISRCTN Registry: ISRCTN93129502, http://www.isrctn.com/ISRCTN93129502 (Archived by WebCitation at http://www.webcitation.org/6Yf5VSyyG).

## Introduction

### Background

The treatment of many forms of congenital heart disease has continued to advance, and primary early repairs of an increasing number of defects are routinely performed (eg, atrioventricular canal, tetralogy of Fallot, transposition of the great arteries). At Bristol Royal Hospital for Children (BRHC) an average of 285 cardiac operations are performed a year, and approximately 75% (ie, an average of 210) require cardiopulmonary bypass (CPB). Despite its widespread use, there is still significant morbidity related to the nonphysiological nature of total CPB [1]. Whole body cooling (ie, hypothermia) is an integral part of congenital cardiac surgery, with most procedures being conducted between 28°C and 30°C, depending on the expected duration and type of operation. The main rationale for body cooling is to protect organs such as the brain, kidneys, and heart from ischemic injury by reducing the metabolic rate and, hence, oxygen consumption [1]. Nevertheless, hypothermia has a number of disadvantages, including detrimental effects on enzymatic function, energy generation, and cellular integrity [1]. Perfusion of the body and the brain at normal body temperature (ie, normothermia) is a potentially more physiological method to maintain the functional integrity of major organ systems, and in recent years there has been an increasing interest in normothermic CPB in adult and pediatric cardiac surgery [2-9]. The concept that normothermic systemic perfusion may confer certain advantages over hypothermic regimes arose fortuitously from adult clinical experience in which an absence of shivering, hemodynamic stability, minimum use of inotropes, and early extubation were observed when patients were not cooled [2]. This led several investigators to study the effects of systemic hypothermia and normothermic perfusion upon cellular and organ function [2,10-14].

In both adult and pediatric cardiac surgery, many of the detrimental effects of CPB on end organ dysfunction were previously believed to be mediated by activation of the inflammatory response [1,15]. One may expect that CPB-related systemic inflammatory response syndrome and multiorgan injury to be enhanced during normothermia, since most enzymatic processes occur optimally at 37°C. Supportive of this notion are clinical studies in adults [16] in which normothermic CPB (35°C-37°C) was associated with significantly elevated levels of inflammatory markers compared to hypothermic CPB (28°C-30°C). Consistent with this, previous animal data have shown that the inflammatory response is reduced by hypothermia [17,18]. However, a conflicting picture is emerging from research. Ohata et al [19] have demonstrated an attenuation of certain inflammatory mediators following warm systemic perfusion (34°C) compared to hypothermic perfusion (28°C). In a clinical study at the Bristol Heart Institute [10,20], normothermic (37°C) perfusion was also associated with attenuation of inflammatory mediator release in the postoperative period, compared to moderately hypothermic (32°C) and hypothermic CPB (28°C). In contrast, others have suggested that induction of a systemic response is not temperature dependent. Rasmussen et al have shown that the release of systemic inflammatory mediators after cardiac surgery in adults was independent of mild hypothermia (32°C) when compared to normothermia (36°C) [21]. A randomized controlled trial (RCT) in 66 children having open heart surgery, who were randomized to either moderate hypothermia (24°C) or mild hypothermia (34°C), found that neither the systemic inflammatory response nor organ injury were influenced by bypass temperature [22]. Eggum et al demonstrated that there were only minor differences in inflammatory marker concentrations between pediatric patients undergoing moderate (25°C) hypothermia and those with mild (32°C) hypothermia during CPB [23]. This evidence was supported by an RCT carried out at BRHC comparing warm (35°C-37°C) and cold (28°C) CPB on simple congenital cardiac malformations, which indicated that both whole body inflammatory response and myocardial reperfusion injury were similar between the 2 groups [24]. In addition, Caputo et al and Eggum et al demonstrated that normothermic CPB was associated with reduced oxidative stress compared with hypothermic CPB. Other researchers have studied the effect of the temperature of the cardioplegia during pediatric cardiac surgery [25,26]. Poncelet et al have taken this a step further by studying the effect of the temperature of the CPB in addition to the cardioplegia in an RCT on 47 children having cardiac surgery [27]. In this study, children were randomized to either mild hypothermia with cold crystalloid cardioplegia (CPB temperature 32°C, cardioplegia at 5°C) or normothermic with intermittent warm blood cardioplegia (CPB temperature 36.5°C). They found no significant difference in the cellular ischemic insult to the heart or in the early and late neurodevelopmental status of the patients. With conflicting evidence arising from clinical trials comprising relatively low numbers of patients and mainly simple cardiac surgery cases, it is difficult to establish whether the induction of a systemic response is temperature dependent and the impact this may have on clinical outcome. This warrants a larger study with clinical outcomes as primary endpoints.

### Aim

The Thermic-2 study (Current Controlled Trials ISRCTN93129502) will compare the clinical effectiveness of normothermic (35°C-37°C) versus hypothermic (28°C) CPB for the repair of common congenital cardiac pathologies. We will test the hypothesis that maintaining the body at 35°C-37°C (normothermia) rather than at 28°C (hypothermia) during pediatric open heart surgery reduces the whole body inflammatory response to the nonphysiological CPB and its detrimental effects on different organ functions, resulting in a better clinical outcome.

## Methods

### Study Design

This study is a single-center, parallel-group open RCT. The study schema is shown in Figure 1.

**Figure 1 figure1:**
[figure not shown]
Study schema showing the participant recruitment pathway.

### Research Approval

Research ethics approval was granted by the National Research Ethics Service Committee South West—Central Bristol (reference 11/SW/0122) in October 2011. The study is registered (ISRCTN 93129502).

### Study Population

All pediatric patients (aged 18 years and younger) having scheduled surgery at the BRHC to repair a congenital heart defect using CPB, represent the target study population and will be screened for eligibility. Patients will be excluded from the study if either: (1) they require deep hypothermic circulatory arrest, (2) they are admitted for an emergency operation (patients with hemodynamic instability who require immediate surgical intervention), or (3) they and/or their next-of-kin do not provide written informed consent. We will also record specific reasons where surgeons are unwilling for the patient to be approached for the study. All reasons for ineligibility will be recorded on the study screening log.

We will aim to approach all next-of-kin (usually parents) and/or patients at preoperative clinics or on admission the day before surgery. Eligible next-of-kin and/or patients will be given a patient information leaflet (PIL), have the study explained to them, and will be given the opportunity to ask questions about the study. They will be given a minimum of 24 hours to consider the study prior to being asked to provide written informed consent if they are willing to participate in the study.

### Randomization

Participants will be randomly assigned in a 1:1 ratio to either the hypothermic group or the normothermic group. Randomization will be stratified by age: 1 month or younger, 1 to 12 months, and older than 12 months. Allocations will be generated by computer using block randomization with varying block sizes. The allocation sequence will be prepared in advance of the study by a statistician independent of the study team. If a participant’s surgery is unexpectedly rescheduled, he/she will retain his/her study numbers and randomized allocation. Access to the allocation will be via a password-controlled secure database. Randomization will take place as close to the start of surgery as possible.

### Study Interventions

Participants will be randomized to receive either hypothermic or normothermic CPB during their surgery into the following groups:

Hypothermic CPB: cardiopulmonary bypass with perfusion at 28°C (control)Normothermic CPB: cardiopulmonary bypass with perfusion at 35°C-37°C (experimental)

### Cardiopulmonary Bypass

All operations will be performed using CPB with ascending aortic cannulation and bicaval venous cannulation (Figure 2). Cold St Thomas’ I-based blood cardioplegic solution (4°C-6°C) will be used for myocardial preservation in all participants (Martindale Pharmaceuticals Ltd) with the following composition: 16 mM MgCl2, 2 mM CaCl2, 20 mM KCl, 147 mM NaCl, and 1 mM procaine HCl. Cardioplegic arrest will be achieved by an antegrade infusion of 110 ml/m^2^/min for 4 minutes. Additional cardioplegia will be administered after 20 minutes of aortic cross-clamping. Intramyocardial temperature will be monitored by means of a temperature probe inserted every 10 minutes into the right and left ventricles during ischemic arrest. For all participants, concomitant rectal, nasopharyngeal, skin, and blood temperatures will be monitored throughout the operation.

**Figure 2 figure2:**
[figure not shown]
Image showing the heart of a child born with an atrial septal defect (ASD). The heart has been emptied of blood, put on cardiopulmonary bypass (CPB), and arrested using the cardioplegia solution, which is injected into the aortic root after the aorta is cross-clamped. CPB is achieved by inserting a superior vena cava (SVC) and an inferior vena cava (IVC) cannula for the venous drainage and an aortic cannula for the arterial perfusion of the body. The right atrium is open and the ASD is clearly visible.

#### Hypothermic CPB

Nasopharyngeal body temperature will be lowered to 28°C. Rewarming will commence at the completion of the anatomical correction. All participants will be rewarmed with a temperature difference of 8°C at the level of the heat exchanger between the blood and the rewarming fluid, and CPB will be discontinued only after the participant is fully rewarmed to 36°C.

#### Normothermic CPB

Nasopharyngeal body temperature will be maintained at 35°C-37°C. Rewarming will only take place in the normothermic group if the body temperature is <36°C and will be discontinued only after the participant is fully rewarmed to 37°C.

### Anesthesia

Induction of anesthesia will be gaseous induction with sevoflurane, administration of neuromuscular blockade using pancuronium and analgesia using bolus dose fentanyl (10 mcg/kg-20 mcg/kg) pre-CPB, and morphine (0.5 mg/kg) during CPB. Maintenance of anesthesia will be with isoflurane. Alpha stat acid-base management will be adopted. Initial anticoagulation will be accomplished with 3 mg/kg to 4 mg/kg body weight of heparin and supplemented as required in order to maintain an active clotting time of ≥480 seconds.

Deviations from this standardized anesthetic technique are permissible under the following conditions:

Intravenous induction using ketamine, propofol, or thiopentone may be used if the anesthetist considers sevoflurane to be unsuitable for induction for the patient.Where pancuronium is not available, vecuronium or rocuronium may be used instead.Propofol instead of isoflurane may be used for maintenance of anesthesia where the anesthetist considers the patient to be at increased risk of awareness.

### Study Center and Surgeons

#### Overview

All surgery will be carried out at BRHC. On average, 210 pediatric cardiac surgery procedures using CPB are performed per year at this center. All the pediatric cardiac surgeons at this center are participating in the study.

#### Primary Outcomes

The co-primary endpoints are (1) duration of inotropic support, (2) intubation time, and (3) postoperative hospital stay (from date of surgery to discharge from cardiac ward). These data will be collected from medical notes and hospital charts.

#### Secondary outcomes

Data will be collected to characterize the following secondary outcomes:

In-hospital mortality and morbidity rates will be recorded.Blood loss and transfusion requirements will be recorded.Preoperative and postoperative echocardiographic (ECG) findings will be recorded.Routine blood gas and blood test results will be recorded.Renal function will be measured by testing urinary albumin, urinary creatinine, retinal binding protein (RBP), N-acetyl-β-glucosaminidase (NAG), and neutrophil gelatinase-associated lipocalin (NGAL) [28-33]. All markers of renal damage will be measured preoperatively and at several time-points postoperatively.Cerebral function will be measured by testing for glial fibrillary acidic protein (GFAP), a serum marker of traumatic brain injury [34,35]. GFAP levels will be measured preoperatively and at several time-points mid- and postoperatively.Regional oxygen saturation of blood in the cerebral cortex will be measured at approximately 15-minute intervals during the operative period using near-infrared spectroscopy (NIRS).Neuropsychological development will be assessed using the NEPSY-II psychometric tool [36]. Neuropsychological assessments will be performed on patients aged between 3-16 years old, preoperatively and at 3 and 12 months postoperatively. These tests are intended as a tool to allow the assessment of both basic and complex aspects of cognition across the following 6 functional domains: attention and executive functions, language, memory and learning, sensorimotor functions, social perception, and visual-spatial processing.Cardiac tissue biopsies from heart tissue discarded during the surgical procedure and considered clinical waste will be analyzed for biochemical markers and RNA analysis on a subset of 32 patients. If available, 4 samples will be collected from each patient in this subset; 2 samples will be collected immediately after institution of CPB and a further 2 samples will be collected 10-15 minutes after reperfusion. Biochemical tests will be performed on the biopsies to determine the presence of a range of important proteins and metabolites, and transcriptional profiling by RNA extraction will be performed with the aim to help establish whether any genomic expression changes associated with hypothermia could be prevented by using normothermic techniques.

### Assessment of Outcomes and Blinding

Participants and their parents/guardians will be blinded to the treatment allocation. Participants will receive the same surgical procedure as if they had not joined the study—with the exception of the temperature of the blood during CPB—and will receive the same surgical care following the procedure. At the start of the operation, the perfusion team is given the treatment allocation in a concealed envelope, asked to follow the study allocation, and record any reasons for protocol deviations. Surgeons, anesthetists, and nurses involved in the operation will be unblinded but the randomization allocation will not be disclosed until after the start of the operation. Because surgeons, anesthetists, and nurses continue to care for participants in the pediatric intensive care unit (PICU) and on the ward, it is difficult to maintain blinding in these locations. Where possible, staff will be blinded to the treatment group to which a participant is assigned. The PICU and ward nursing teams, while not being actively informed of the patient’s study allocation, could become unblinded because they have access to the anesthetic and perfusion charts that must be stored in the medical notes. However, it is unlikely that the nursing team would check the temperature at which the operation was performed or alter the patient’s after-care since the temperature during CPB would not have any implications on the postoperative management of the patient.

The primary endpoints of duration of inotropic support, intubation time, and postoperative hospital stay should all be objective outcomes and were chosen primarily as they are clinically meaningful to the patients and surgeons. While these outcomes could potentially be influenced by the clinical care team, the care team must not only adhere to strict protocols and guidelines, but there is also not a strong expectation that either arm of the study would be more beneficial to the participant; therefore, performance and detection bias are minimized.

Outcomes such as in-hospital mortality and morbidity, blood loss and transfusion requirements, routine blood gas, blood sample/test results, and regional oxygen saturation of blood in the cerebral cortex are objective outcomes and will be recorded directly from medical notes, PICU charts, and electronic records.

Preoperative and postoperative ECG findings involve some level of subjectivity and judgement; however, ECGs will be interpreted by a cardiologist blinded to treatment allocation. Renal function analysis, cerebral function analysis, cardiac tissue function analysis, and NEPSY-II test administration are not part of routine care, and assessment will be carried out by blinded researchers. Reasons for noncompletion of tests or assays will be recorded.

### Data and Sample Collection Schedule

The schedule for data and sample collection is shown in Table 1.

**Table 1 table1:** Schedule of data and sample collection.

Data and samples collected	Preoperative	Perioperative				Postoperative									
		Pre-surgery	Start of CPB^a^	10m post CPB	XC^b^ removal	XC+ 30m^c^	XC+ 2h^d^	XC+ 4h	XC+ 6h	XC+ 24h	XC+ 48h	XC+ 72h	Discharge	3 mo^e^	12 mo
Eligibility	✓^f^														
Consent	✓														
NEPSY-II^g^	✓													✓	✓
Baseline data	✓														
Randomization		✓													
Routine blood gases		✓			✓	✓	✓		✓	✓					
Routine blood samples		✓					✓^h^			✓	✓	✓			
GFAP		✓			✓	✓	✓		✓	✓	✓				
NIRS		✓^i^													
Urine samples		✓			✓^j^			✓		✓	✓				
Cardiac tissue biopsies			✓	✓											
Operative details		✓	✓	✓	✓^k^										
Clinical outcomes													✓		
Safety data										✓	✓	✓	✓	✓^l^	✓

^a^CPB: cardiopulmonary bypass

^b^XC: cross clamp

^c^m: minutes

^d^h: hours

^e^mo: months

^f^✓ = data/sample collected

^g^Only performed on participants eligible for NEPSY-II psychometric assessment.

^h^Routine blood samples taken on admission to PICU.

^i^As many NIRS results will be recorded as are taken in theater.

^j^Urine samples taken at cross-clamp removal/end of CPB.

^k^Operative details are recorded on cross-clamp removal and chest closure.

^l^Hospital admission questionnaire only administered if 3-month NEPSY administered.

### Participant Follow-Up

All primary and most secondary outcomes are assessed while the participant is in hospital following their surgery. For NEPSY-II eligible patients, NEPSY assessments will take place at 3 months and 12 months postoperatively (Figure 1 and Table 1). Safety data will also be collected at these visits. For participants that are not eligible for NEPSY-II assessments, follow-up for safety will occur at 12 months postoperatively by postal questionnaire. Active participation for all patients will cease either at their final NEPSY-II assessment or on return of the follow-up postal questionnaire, 12 months post operatively.

### Sample Size

#### Primary Outcomes

The geometric mean postoperative hospital stay in our institution is estimated to be 6.2 days, with standard deviation (on the logarithmic scale) of 0.4. A sample size of 100 participants per group would be sufficient to allow us to detect a clinically relevant 1 day or greater reduction in mean length of stay with 90% power, assuming a 5% level of statistical significance (2-tailed).

Using estimates for ventilation time and duration of inotropic support from our institution, a total sample size of 200 would also be sufficient to detect a 16% reduction in ventilation time (3 hours), and a 13% reduction in inotropic support (4.7 hours). All these differences represent clinically relevant reductions.

In an earlier RCT comparing the same 2 interventions carried out at our institution (Thermic-1), 59 participants were recruited. The primary outcomes for this earlier study were biochemical markers of organ injury, but clinical outcome data were also collected. For the current study (Thermic-2), 141 participants have been recruited. The clinical data from the 2 studies will be combined for assessment of the clinical outcomes, giving a total sample size of 200 participants for analysis.

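### On the inputs as printed, 100 per group gives about 87% power for a 1-day reduction in postoperative stay, not the stated 90%

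*Protocol article*

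**What the plan says.** The calculation is in the Protocol article under Sample Size, Primary Outcomes. The starting point is stated as "The geometric mean postoperative hospital stay in our institution is estimated to be 6.2 days", "with standard deviation (on the logarithmic scale) of 0.4". The conclusion drawn is: "A sample size of 100 participants per group would be sufficient to allow us to detect a clinically relevant 1 day or greater reduction". The same sentence gives 90% as the power and 5%, two-tailed, as the significance level. Under Randomization, "Participants will be randomly assigned in a 1:1 ratio", so the two groups are meant to be equal.

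The section then says that the same total of 200 also suffices for ventilation time and inotropic support. It explains that the 200 is made up of 59 participants from Thermic-1 and 141 from Thermic-2. Of the three co-primary outcomes, postoperative stay is the only one for which both the baseline and the SD are printed, so it is the only one whose power can be checked.

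**The concern.** Every ingredient of the calculation is given: baseline, log-scale SD, difference, group size, significance level, sidedness and power. A reader can therefore recompute the result, and it does not come out at 90%. This is not a matter of something left to a fuller document, because inputs and result stand together and disagree.

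What is at stake is how a null result for postoperative stay would be read. The authors call a 1-day reduction clinically relevant and in effect state a 10% chance of missing it. On the printed inputs that chance is 12.5% to 12.8%.

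**Working it through.** **Inputs** (all from Sample Size, Primary Outcomes, except the allocation ratio, which is from Randomization)

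- Control geometric mean: 6.2 days
- SD on the log scale: 0.4 (natural logs assumed)
- Difference: 1 day, so 6.2 to 5.2 days
- 100 per group, allocated 1:1
- Two-sided 5%: z = 1.960. Stated power 90%: z = 1.2816

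**Step 1. Effect on the log scale.** ln(6.2/5.2) = 0.1759. In SD units, 0.1759/0.4 = 0.44.

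**Step 2. Power with 100 per group.** The standard error of the difference is 0.4 × √(2/100) = 0.05657. Then 0.1759/0.05657 = 3.109, and Φ(3.109 − 1.960) = Φ(1.149) = 0.875. The noncentral t-test gives 0.872. The stated figure is 0.90, so the shortfall is 2.5 to 2.8 percentage points.

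**Step 3. Group size for 90% power.** n = 2 × [(1.960 + 1.2816) × 0.4/0.1759]² = 108.7, so 109 per group (218 in total). The t-test gives 109.65, so 110 per group (220 in total). This is 9% to 10% above the stated 100.

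**Step 4. Difference detectable with 90% power at 100 per group.** (1.960 + 1.2816) × 0.05657 = 0.1834 on the log scale. The reduction is 1 − exp(−0.1834) = 16.8%, and 6.2 × 0.168 = 1.04 days.

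**Step 5. SD at which 90% holds for exactly 1 day.** 0.1759/[√(2/100) × 3.2415] = 0.384.

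**Step 6. Attempts to recover the stated 90%** (normal approximation, 100 per group)

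| Variant | Power |
|---|---|
| Printed inputs, two-sided 5% | 87.5% |
| Reduction of 16% instead of 1 day | 86.9% |
| Reduction of 17% (1.05 days) | 90.9% |
| One-sided 5% (the article says two-tailed) | 92.8% |
| Baseline 6.15 days, log-SD 0.4 | 88.0% |
| Baseline 6.2 days, log-SD 0.38 | 90.5% |
| Baseline 6.2 days, log-SD 0.42 | 84% |

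No two-sided calculation for a 1-day reduction at a log-SD of exactly 0.4 reaches 90%. Reading the SD as base-10 does not help: log10(6.2/5.2) is smaller than 0.1759 and would be set against the same 0.4, so power would be lower. Rounding of the baseline alone is not enough either. Two things do bring the figure back: an SD of about 0.38 that was printed as 0.4, or a detectable difference of 1.04 days that was printed as 1 day.

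**The case against.** The strongest reply is that the gap lies within the precision of the printed inputs. The log-SD is given to one decimal. At 6.2 days, an SD of 0.35 gives 94.5% power and one of 0.449 gives 79.1%, and both would print as 0.4. The stated 90% lies inside that range. A detectable difference of 1.04 days would also naturally be written as 1 day. This stands. It means that the article cannot be said to have got its power wrong, only that the figure does not follow from what is printed. But rounding works in both directions, so it does not establish the 90% either.

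A second reply is that the analysis plan adjusts for age group (Statistical Analyses, Plan of Analysis). Moving from an SD of 0.40 to 0.384 needs age group to explain 1 − (0.384/0.40)² = 8% of the log-scale variance, which is possible. The sample size section does not invoke this gain, so it does not account for the 90%. It does mean that 87% describes an unadjusted comparison.

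A reader might point to the words "detect a clinically relevant 1 day or greater reduction in mean length of stay" and say that larger differences have more power. They do, but 1 day is the smallest difference for which 90% is claimed, so the check belongs there.

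Three stronger readings are tempting, and the document does not support them:

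- *The effect is on the arithmetic mean.* The effect is called simply a mean, and on an arithmetic reading power would be lower still. But the sentence before it defines the quantity as a geometric mean with a log-scale SD, and the natural reading carries that over.
- *The 200 should have been inflated for missing data or for departures from the allocated temperature.* The article is a condensed account. Participant Follow-Up says that all primary outcomes are assessed in hospital, and nothing says that the 1-day effect assumes full adherence. This is no defect of the calculation.
- *This calculation alone fixed the target of 200.* The article presents the total as also serving ventilation time and inotropic support, so that inference goes beyond the text.

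**Conclusion.** The point holds as a minor inconsistency. On the inputs as printed, power for a reduction in geometric mean stay from 6.2 to 5.2 days is about 87%, not 90%. The 90% would require 109 to 110 per group, a reduction of about 1.04 days, or an unrounded log-SD of about 0.38. The result rests on natural logs, equal groups, all 200 participants contributing, and an unadjusted two-sample comparison on the log scale.

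Nothing here shows that the trial is materially underpowered or that its design or analysis should change. The article does not reveal whether the cause is a rounded SD, a rounded difference or a slip, and the correction should not presume which.

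**What to change.** Change one sentence under Sample Size, Primary Outcomes, in one of two ways:

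- If the SD used was 0.40: state that 100 per group gives about 87% power to detect a reduction in geometric mean stay from 6.2 to 5.2 days (log-SD 0.40, two-sided 5%), or 90% power for a reduction of about 1.04 days (16.8%).
- If the SD used was about 0.38: keep the 90% and print the SD to two decimals, so that a reader can reproduce it.

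The sponsor should go back to the calculation that was run and choose accordingly. Printing 87% without that check would introduce an error if the SD was really about 0.38. The cost is one sentence and, in the first case, a slightly less favourable figure. Recruitment is already complete, and no extra participants are needed.
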